## Abstract

High levels of inflammatory markers have been associated with a greater deterioration of renal function and cardiovascular morbidity and mortality. For its part, physical exercise has been shown to be beneficial in improving the functional, psychological, and inflammatory states of patients with chronic kidney failure (CKF) undergoing haemodialysis (HD) treatment, improving their health-related quality of life. In recent years, virtual reality (VR) has been studied and described as an effective and safe tool that improves patients’ adherence to exercise programs. For these reasons, we propose to analyse the effect of VR exercise on the functional, psychological, and inflammatory states of patients on HD, as well as their levels of adherence to exercise, and compare them with static pedalling exercises. We will randomise 80 patients with CKF into two blind groups: an experimental group, which will carry out an intradialytic exercise program with non-immersive VR (n = 40), and a control group, which will exercise with a static pedal (n = 40). Functional capacity, inflammatory and phycological status, and exercise adherence will be analysed. Higher levels of adherence to exercise are expected in the VR group, which will have greater effects on the patients’ functional capacity and psychological and inflammatory status.

## 1. Introduction

Chronic kidney disease (CKD) represents one of the main public health problems [1]. It affects one in seven adults in Spain, being more prevalent in men (23.1% in men vs. 7.3% in women), in older populations (4.8% in subjects aged 18–44, 17.4% in subjects aged 45–64, and 37.3% in subjects ≥ 65 years), and in subjects with cardiovascular disease (39.8% in subjects with cardiovascular disease vs. 14.6% in subjects without cardiovascular disease) [2].

Globally, about 500 million adults suffer from CKD [3]. Although only 1% of these patients require renal replacement therapy (RRT) through dialysis or kidney transplantation, this condition leads to a marked reduction in life expectancy. Moreover, it constitutes one of the most expensive treatments for chronic diseases, consuming 5% of the budget of the healthcare system [4].

Patients with CKD present persistent low-grade inflammation, which is recognised as an important component in the pathophysiology of CKD and is responsible, in part, for cardiovascular mortality and general mortality, in addition to contributing to the development of protein-energy wastage [5].

There is an inversely proportional relationship between the glomerular filtration rate (GFR) and plasma levels of inflammatory markers caused by the presence of oxidative stress, endothelial dysfunction, and vascular calcification [6], together with additional factors such as periodontitis, accumulation of circulating cytokines, non-biocompatible haemodialysis membranes, excess volume, and subclinical infections of vascular access routes [7].

Different biomarkers of inflammation have been identified with predictive value in CKD/chronic kidney failure (CKF). In a large multicentre international database of HD patients, C-reactive protein (CRP) predicted mortality with an accuracy comparable to that of albumin and superior to ferritin and white blood cell (WBC) count [8]. However, it appears that interleukin 6 (IL-6) is a better predictor of cardiovascular and all-cause mortality than CRP and other cytokines, such as tumour necrosis factor alpha (TNF-α), interleukin 1-beta (IL-1β), and interleukin 18 (IL-18) [9].

On the other hand, adhesion molecules also play an important role in inflammatory processes. These are proteins located on the cell surface and are involved in the attachment of leukocytes, endothelial cells, and other extracellular matrices. The main groups of adhesion molecules are the selectins, the integrins, the immunoglobulin superfamily, and the cadherins. In CKD, the most widely studied adhesion molecules associated with inflammation, cardiovascular risk, and mortality are intercellular adhesion molecules-1 (ICAM-1) and vascular adhesion molecules-1 (VCAM-1). Increased levels of these markers predict overall mortality and cardiovascular mortality in patients with CKD not undergoing HD and in patients undergoing HD [10].

The existence of a relationship between endothelial-dependent vasodilation and the markers of inflammation in uremic patients has also been demonstrated, suggesting a pathogenic role of inflammation in the endothelial dysfunction associated with uraemia [11].

Given that cardiovascular disease (CVD) and infection are the main causes of morbidity and mortality in patients with CKD [12,13], the immune dysfunction that accompanies CKD represents a primary target for improving the results of therapeutic interventions.

Physical exercise has been widely studied in recent years, having demonstrated its potential as a therapeutic tool in patients with CKF on HD [14,15]. Regular physical exercise of moderate intensity has a beneficial effect, improving immune function and exerting anti-inflammatory effects [16,17,18]. This modality of exercise has been associated with modulating cytokines, lowering levels of pro-inflammatory cytokines, and increasing levels of anti-inflammatory cytokines [19], contributing, in part, to reducing the risk of infections and CVD [16,17].

The chronic inflammatory state and the immune imbalance that patients with CKF present leads to a loss of strength and muscle mass, impairing the functional capacity of these patients. Physical exercise can modify the inflammatory response through the mechanical stress that it produces on the muscle fibre, improving the processes of adaptation, remodelling, and causing the structural and functional repair of the skeletal musculature [20,21,22]. In addition, physical activity can produce a transient increase in endogenous glucocorticoids, leading to a selective decrease in circulating CD16+ monocytes [23]. On the other hand, it has been shown that exercise regulates Toll-like receptors (TLRs) dependent on inflammation, decreasing their levels, which reduces the cellular expression of TLR4, attenuating the inflammatory response induced by lipopolysaccharides [24].

Similarly, patients with CKF on HD have very high levels of sedentary lifestyle, which exacerbates their chronic inflammatory state and increases the loss of muscle mass and strength. This situation, associated with their high cardiovascular (CV) morbidity and mortality, places these patients in a vicious cycle where exercise can bring them great benefits [25].

Physical exercise has been widely shown to improve the functional capacity of patients with CKF, either through intradialytic exercise [26] or home exercise programs [27].

Psychological problems are also very frequent in these patients, presenting a prevalence of depression of 27%, which is associated with impaired quality of life and increased mortality. Besides, there is evidence of an association of higher pro-inflammatory and lower anti-inflammatory cytokine levels and depressive symptoms in patients with CKD/CKF [28]. In this sense, exercise offers great benefits to improve both inflammatory levels and associated depressive symptoms [18,29].

In recent years, virtual reality (VR) has been recognised as a new and effective tool to promote physical activity and healthy behaviour, and its use in health promotion is increasing [30]. Recent research has shown that VR enhances the psychological benefits of exercise and increases the likelihood of greater long-term exercise adherence [31].

Recently, the integration of VR into traditional physical exercise and rehabilitation programs has aroused great interest in the fields of kinesiology and public health. Using VR, it is possible to intensify repetitive tasks and increase visual and auditory feedback, which makes it a novel and attractive therapeutic tool that can be combined with traditional physiotherapy, as it is safe and effective for the patients who use it [32].

Researchers have recently begun to investigate whether the beneficial effects that VR has been shown to have in exercise programs for other populations can be extrapolated to patients with CKF undergoing HD treatment. There are five clinical trials published to date [33,34,35,36,37], the results of which show that the application of VR exercise during HD improves physical function and reduces fatigue and depression in these patients.

In 2019, Segura-Orti and García-Testal conducted a review that reinforced these results, concluding that intradialytic exercise with VR is safe and improves physical function and health-related quality of life in patients on HD. They also concluded that this exercise can be performed safely during the last hours of the HD session [38].

Along the same lines, another review by Olumuyiwa et al. concludes that the use of VR during HD treatment significantly improves the levels of physical activity and fatigue in patients with CKF, as well as increases the levels of adherence and commitment to HD treatment, without the appearance of adverse effects [39].

Currently, only one study has analysed the effect of VR exercise on depression levels in patients on HD, whereas the effect of VR exercise on the inflammatory status of these patients has not been studied at all. It could be expected that the beneficial effects on inflammation are comparable to those obtained with conventional exercise [19], and their psychological state also improves. Therefore, we plan to carry out a study of these characteristics with the aim of determining the effectiveness of an intradialytic exercise program with VR on inflammatory markers, in addition to delving into its effect on functional capacity and psychological state. As a secondary objective, we intend to analyse the levels of adherence to the exercise program and compare the results obtained for all the variables to those of a group that performs intradialytic static pedal exercise.

## 2. Materials and Methods

### 2.1. Type of Study

The study will be carried out prospectively between June 2023 and June 2024. It is an experimental, controlled, blind, and randomised study, whose methodology complies with the CONSORT standards for clinical trials. (CONSORT 2010 flow diagram, Figure 1). This protocol report follows the Standard Protocol Items: Recommendations for Interventional Studies (SPIRIT) 2013 checklist [40].

The study has passed the responsible research evaluation of Miguel Hernandez University of Alicante, with assigned code TFM.MMC.EJPP.EMO.220221, and later registered in ClinicalTrials.gov (NCT05606484) (accessed on 25 September 2022).

Before the study begins, the approval of the ethics committee of the Hospital General Universitario de Alicante Doctor Balmis will be requested.

### 2.2. Study Population

#### 2.2.1. Population Sample

The population sample will be selected from the Haemodialysis Unit of the General University Hospital of Alicante Doctor Balmis, which is visited by patients with terminal CRF, through convenience sampling. The following inclusion and exclusion criteria will be applied:

##### Inclusion Criteria [23,34]:

Patients with CKF in a stable clinical situation who have been on HD treatment for at least 3 months.

##### Exclusion Criteria [23,34]:

Had a myocardial infarction in the 6 months before the start of the study;Suffered unstable angina at rest or during exercise;Have cerebrovascular diseases (such as transient ischemia or stroke);Present amputation of lower limbs above the knee without prothesis;Present a musculoskeletal or respiratory pathology likely to worsen with exercise;Present an inability to carry out functional assessment tests;Present visual or cognitive impairments that affect the ability to use the VR equipment or understand the VR exercise.

#### 2.2.2. Randomisation of the Sample

To avoid potential biases that could convolute the results of the program based on sex or age, the groups will be homogeneous in these characteristics. For this, randomisation will be carried out by blocks of sex and age (www.randomization.com), whose randomisation sequence will be hidden (OSA).

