### 2.8. Statistical Analysis

The sample size of the study was calculated using the statistical program G-Power (analysis of variance (ANOVA): repeated measures, within/between interaction), assuming a type I error or α of 0.05 (95% confidence interval), a statistical power of 0.80 (type II or β error), and an effect size of 0.25 (mean), requiring the inclusion of 24 patients to ensure the external validity of the study. Considering that there may be losses during the study follow-up, 80 patients will be included: 40 in the control group and 40 in the intervention group.

Intention-to-treat statistical analysis will be performed using the statistical program SPSS 23.0 for Windows (SPSS Inc, Chicago, IL, USA).

The normal distribution of the groups will be verified through the chi-square and Mann–Whitney U tests for correct randomisation.

A mixed two-way ANOVA test will be used to analyse the effect of the VR exercise on functional variables and inflammatory variables in each study group and to analyse the differences between the two groups.

Data will be presented as mean ± standard deviation, setting statistical significance at *p* < 0.05.

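### Randomisation is blocked by sex and age but the two-way ANOVA omits both, which costs some precision: always in the group main effect if they predict level, in the group-by-time test only if they predict change

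*Protocol article*

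**What the plan says.** Section 2.2.2 (Randomisation of the Sample) makes the arms alike on sex and age: "randomisation will be carried out by blocks of sex and age". The reason given is "To avoid potential biases that could convolute the results of the program based on sex or age". Age bands and block size are not given.

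Section 2.8 (Statistical Analysis) names the model: "A mixed two-way ANOVA test will be used to analyse the effect of the VR exercise on functional variables and inflammatory variables". The same model is to serve "to analyse the differences between the two groups". In a two-arm trial measured before the program and at 12 weeks (Section 2.4), the two ways are group and time. No sex term, age term, other covariate or stratified analysis is mentioned anywhere in the article. The sample size is based on the within/between interaction, which here is group by time.

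**The concern.** The design treats sex and age as able to distort the results, while the named analysis ignores them. Blocking removes chance imbalance in sex and age between arms, so the real sampling variance of the arm difference falls. A model without those factors still counts their variation as residual error and reports a standard error for a trial that was not blocked. Intervals are then too wide and p-values too large.

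At stake is precision. Both arms exercise the same muscle groups at the same perceived exertion, so the difference between them may be small, and precision paid for at randomisation should not be discarded in the analysis. How much is lost depends on which term of the ANOVA is read and on what sex and age predict.

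**Working it through.** **The plan's own figure.** For the within/between interaction with *k* = 2 groups and *m* measurements at correlation ρ, λ = f²·N·m/(1−ρ), with (k−1)(m−1) and (N−k)(m−1) degrees of freedom. Section 2.8 gives f = 0.25 (read as Cohen's f), α = 0.05, power 0.80 and N = 24; *m* and ρ are not stated. N = 24 is reproduced with m = 4 and ρ = 0.5 (λ = 12, power 0.816). With the protocol's two measurements and ρ = 0.5, the requirement is 34. The planned 80 covers both, so this does not affect the present point.

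**Step 1: what the interaction tests.** With two measurements, the group-by-time F test is the two-sample t-test on change (12 weeks minus baseline). A sex or age effect that is the same at both times cancels in the change. Only an effect on the change remains in the residual.

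**Step 2: size of the interaction test.** Let R² be the share of change-score variance explained by the strata. The documents give no value, so a range is assumed. After stratified blocking, the unadjusted test has a true size of about 2·[1 − Φ(1.96/√(1−R²))]. For R² = 10%, 1.96/√0.90 = 2.07, which gives 3.9%. For R² = 20%, 1.96/√0.80 = 2.19, which gives 2.8%.

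A simulation checked this with assumed inputs: 80 patients, four equal sex-by-age strata and permuted blocks of 4. It used 12,000 null trials per row for size and 6,000 per row for power. The power columns use a difference of 0.634 SD of change, chosen because it gives about 80% power at N = 80; it is not in the documents.

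| R² of change (assumed) | Size, formula | Size, strata omitted | Size, strata included | Power, omitted | Power, included |
|---|---|---|---|---|---|
| 0 | 5.0% | 5.0% | 5.0% | 0.81 | 0.80 |
| 5% | 4.4% | 4.6% | 5.2% | 0.80 | 0.82 |
| 10% | 3.9% | 3.9% | 5.1% | 0.81 | 0.84 |
| 20% | 2.8% | 2.7% | 4.9% | 0.83 | 0.88 |
| 30% | 1.9% | 1.9% | 4.9% | 0.85 | 0.92 |

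**Step 3: sex and age affect level only.** Let the strata explain 30% of the level variance and none of the change, with a correlation of 0.5 between the two measurements (assumed). The interaction then runs at 4.9%, whether or not the strata are in the model.

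**Step 4: the group main effect.** This term compares the average of the two measurements, whose variance is (1+ρ)/2 = 0.75 of a single value. The strata's share of it is 0.30/0.75 = 0.40, and 1.96/√0.60 = 2.53 gives a size of 1.1%; the simulation also gives 1.1%. As ρ rises towards 1, the share falls to 0.30 and the size rises to 1.9%. The direction is the same throughout.

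**Step 5: power at the protocol's effect size.** At f = 0.25, N = 80, m = 2 and ρ = 0.5, λ = 0.0625 × 80 × 2/0.5 = 20 and the power is 0.993. With strata that explain 10% or 20% of change variance in the model, λ becomes 20/0.90 = 22.2 or 20/0.80 = 25, and the power is 0.996 or 0.999. Because λ = N·d²/4 for a change difference of d SD, λ = 20 means d = 1.0. The larger gains in the table therefore concern a smaller difference than the one the protocol planned for.

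**The case against.** The strongest objection is that the interaction is the test on which the trial was sized, and in it each patient is their own control. That walking, sit-to-stand and balance depend on age and sex is a statement about how well people perform, and a stable difference of that kind cancels. This stands. A reader might infer that every test in the plan runs at 2% to 4%, and that the functional outcomes suffer most. The documents do not support that: they give no figure for how far sex or age predicts the 12-week change, and the stated worry about the results of the program is too general to supply one.

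It is also fair to say that power at the planned effect is already near its ceiling, that age bands and block size are unstated (sparse strata would balance less well and weaken the effect), and that covariate lists are often left to an analysis plan, which is not shown here. Naming group and time as the two ways does not expressly exclude covariates.

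What remains is narrower. The article does name a model, and that model has no place for the factors the trial randomises by. It does not say which term answers the between-group question, so the group main effect cannot be set aside. That term is conservative whenever sex or age predicts level.

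**Conclusion.** The point holds as a modest loss of precision. The group main effect is conservative if sex or age predicts the level of the outcome: about 1% to 2% true type I error if they explain an assumed 30% of level variance and the measurements correlate at 0.5 or more. The group-by-time interaction is conservative only so far as they predict change: about 3.9% and 2.8% for an assumed 10% and 20% of change variance, and about 5% if they affect level only.

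These figures assume four equal strata, small blocks and complete data. It would be wrong to read the omission as a threat to validity: the error is towards too few rejections, so there is no added risk of a false positive. At f = 0.25 with 80 patients, power hardly changes. The change is worth making because it costs almost nothing, and it matters most if the true difference between the arms is smaller than planned.

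**What to change.** In Section 2.8, for each continuous outcome, state that the arms are compared on the 12-week value by ANCOVA, with the outcome's baseline value and the randomisation strata (sex and age) as covariates. This brings the type I error back to about 5% in every setting examined.

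If the mixed ANOVA is kept, include sex and age together with their interactions with time. Entered only as between-subject main effects, they leave the group-by-time test unchanged when data are complete. In either case, say which estimate answers the between-group question.

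The cost is two to four degrees of freedom out of about 78 (80 − 2): two for sex and age in years, three for four strata, and one more for baseline in the ANCOVA. Both variables must be known in order to randomise, so no new data are needed. If sex and age predict nothing, almost no power is lost (0.81 without the strata against 0.80 with them, at a difference of 0.634 SD). The ANCOVA does replace the named model, so the statistical section would need rewording to match.

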#### 2.2.3. Description of the Intervention

An intradialytic exercise program with non-immersive VR will be carried out for 12 weeks with the aim of improving the functional capacity of patients with CKF, as well as their psychological state (decreased anxiety and depression) and inflammatory state (decreased inflammatory markers IL-6, TNF-α, CRP, ICAM-1, and VCAM-1). For its execution, a sample of 80 subjects from the Haemodialysis Unit of the Balmis Hospital in Alicante will be selected, and the sample will be randomized into two groups (intervention group and control group). The intervention group (n = 40) will perform intradialytic exercise with non-immersive VR. The control group (n = 40) will perform intradialytic exercise with a static pedal.

As the health benefits of exercise in patients with CKF have been widely demonstrated [17,18,19], it would not be ethical to deprive one of the groups of exercising. Therefore, it has been decided that the control group will perform an intradialytic exercise with a static pedal, which will exercise the same muscle groups as in the intervention group with VR.

### 2.3. Exercise Program

The nursing staff from the Haemodialysis Unit and several physiotherapists from the Rehabilitation Unit of the Doctor Balmis General Hospital in Alicante will be instructed at the beginning of the study, so they become thoroughly familiar with the characteristics of both exercise programs (the VR exercise program and pedal exercise program). Later, they will be the ones who supervise and direct the exercise programs during the study.

During the two weeks before the start of the intervention, a test period will be carried out as a first contact, during which the nursing staff will implement the exercise programs to familiarise themselves with the material that the patients will use and to resolve possible doubts that may arise during the execution of each exercise. This trial period will be supervised by the specialist physiotherapist in charge of training the hospital’s nursing staff and physiotherapists.

Additionally, with the aim of improving the levels of adherence to the exercise program by the patients, a psychologist specialised in managing barriers during exercise in special populations will be assigned. They will give a talk to the staff in charge of supervising the intervention about the development of new strategies that help maximise levels of adherence to the program.

The exercise program will last for 12 weeks, with a frequency of three weekly exercise sessions of 30 min each. Exercise will take place during the first two hours of HD treatment [27] and patients will be instructed to exercise as independently as possible. Heart rate and blood pressure will be recorded before and after each session.

